### Statistical analysis plan

#### Sample size and power calculations

The formula for calculating the required number of patients is that used for a cluster-randomized controlled trial design [21]. The calculation is based on an overall maternal mortality rate of 1.5% in the pre-intervention phase and an expected reduction of 30% in maternal mortality in the hospitals of the intervention group, in comparison with the control group. This rate was estimated as an approximate average of stratum-specific rates, which ranged from 0.3% to 2.7%, observed in Senegal in a pilot study in 2004-2005 [16]. Taking into consideration a minimum of 830 women included per hospital, the number of patients required was calculated for an odds ratio of 0.70 and for an intra-cluster correlation coefficient (ρ) of 0.001. The value of 0.001 can be considered conservative given the results of the WHO global survey on maternal and perinatal health [22]. The calculation shows that a total of 38,205 patients and 46 hospitals (38,205/830) allows us to achieve a power of 82% to detect a 30% reduction in the overall rate of maternal mortality between the two groups (OR = 0.70) with 2-sided significance test at α = 0.05 and with ρ = 0.001 (ACluster-design^® ^2005, version 2.0, World Health Organization).

According to service statistics available for 2006 and collected for the 46 hospitals in the study, the expected number of deliveries is 96,941 (mean cluster size = 2300; minimum = 830; maximum = 8600), 50,144 in Senegal and 46,797 in Mali. We identified 1,067 trained professionals working in these facilities, 536 in Senegal and 531 in Mali.

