#### Statistical analyses

Binary outcome (maternal death) will be measured for each woman included in the study, while the unit of randomization and intervention is the hospital, to avoid contamination bias. A first descriptive analysis will allow us to verify, in the pre-intervention phase, the comparability of the groups in terms of the characteristics of the centres and of the patients included. The primary analyses will take into account the inter- and intra-cluster variability and adjust the intervention effect for stratification variables (country and hospital type). To adjust the estimate of variance in the intervention's effect on the interdependence of the events measured (maternal death or not) among the patients of a given hospital, we will use the Generalized Estimating Equations (GEE) approach which generalizes logistic regression to cluster data [24]. The interchangeable structure of the residual covariance matrix will be used to represent intra-cluster correlations. In secondary analyses, we will use the multivariable GEE model to adjust the effect of the intervention for those patient-level or hospital-level variables that show a marked imbalance between the two arms of the trial. The same approach will be used for secondary assessment criteria. In all the analyses, the effect of the intervention will be estimated using the odds ratio (95% CI) from the GEE model and tested by one-tailed Wald testing (α = 0.05) [24].

The preliminary analyses will verify whether the intervention's effect varies according to country using the likelihood ratio chi-square test with one degree of freedom for country-intervention interaction. If the test does not reject the null hypothesis at α = 0.05, the interaction will be eliminated from the final model, which will allow us to assess the overall effect of the intervention. On the other hand, if the interactions are statistically significant, the sub-group analyses will assess the effects of the intervention separately for each country, with a power less than 90%. A similar approach will be used to test whether the effect of the intervention depends: (i) on the overall rate of maternal mortality in the pre-intervention phase (Year 1); (ii) on changes in maternal mortality within the intervention period; or (iii) on hospital type.

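### The plan tests the country-by-intervention interaction with a likelihood ratio chi-square, but the only model it names, GEE, has no likelihood to supply one, and the result decides whether an overall or a country-specific effect is reported.

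*Protocol article*

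**What the plan says.** All of this is in the protocol article, section Statistical analyses, unless noted.

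- Model: "we will use the Generalized Estimating Equations (GEE) approach which generalizes logistic regression to cluster data". Working correlation: "The interchangeable structure of the residual covariance matrix will be used to represent intra-cluster correlations".
- Adjustment: the primary analyses "adjust the intervention effect for stratification variables (country and hospital type").
- Effect measure in every analysis: "the effect of the intervention will be estimated using the odds ratio (95% CI) from the GEE model", with the effect "tested by one-tailed Wald testing (α = 0.05").
- Country interaction: tested "using the likelihood ratio chi-square test with one degree of freedom for country-intervention interaction". If it is not significant at 0.05, the term is dropped and an overall effect is estimated. If it is significant, effects are assessed separately by country, and the article puts the power of those analyses below 90%.
- Other modifiers: "A similar approach will be used to test whether the effect of the intervention depends" on Year 1 maternal mortality, on changes in mortality during the intervention period, or on hospital type.

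The article names no random-effects logistic model or other likelihood-based model for clustered data. The Randomization and allocation section defines three hospital types. The Sample size and power calculations section uses an ICC of 0.001 and 830 women per hospital, and describes the expected sizes as "mean cluster size = 2300; minimum = 830; maximum = 8600".

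**The concern.** A likelihood ratio statistic is twice the difference between two maximised log-likelihoods. GEE specifies a mean model and a working correlation and solves estimating equations; it does not maximise a likelihood. The article therefore fixes a test that cannot be taken from the model it fixes, so this is a mismatch between two stated choices and not a missing detail.

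The mismatch matters because the test is a gate: its result decides whether the final model carries one overall effect or two country effects. An analyst told to produce a likelihood ratio chi-square could most readily take it from ordinary logistic regression, which treats women in the same hospital as independent. That test would be too liberal, and chance differences between hospitals would be read as a difference between Mali and Senegal.

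**Working it through.** **1. The plan's own figure.** Inputs from Sample size and power calculations: control rate 1.5%, odds ratio 0.70, 38,205 women, 46 hospitals, 830 per hospital, ICC 0.001, two-sided 0.05.

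- Intervention rate: odds 0.015/0.985 × 0.70 give 1.055%.
- Design effect: DE = 1 + (830 − 1) × 0.001 = 1.829.
- Effective number per arm: (38,205/2)/1.829 = 10,444.
- Standard error of the difference: √[(0.015 × 0.985 + 0.01055 × 0.98945)/10,444] = 0.00155. Then z = 0.00445/0.00155 ≈ 2.87 (unrounded inputs), and power = Φ(2.87 − 1.96) ≈ 81.7%.

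The stated power is 82%, so the plan's figure reproduces, and a design effect of 1.83 is built into the plan.

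**2. A likelihood ratio test that ignores clustering.** A 1-df test that treats women as independent understates the variance by about the factor DE. Its actual rejection rate with no true interaction is approximately P(|Z| > 1.96/√DE).

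| Women per hospital | DE at ICC 0.001 | 1.96/√DE | Rejection rate |
|---|---|---|---|
| 830 (planning minimum) | 1.83 | 1.449 | 15% |
| 2,107 (96,941/46) | 1 + 2,106 × 0.001 = 3.11 | 1.112 | 27% |
| 2,300 (stated mean) | 1 + 2,299 × 0.001 = 3.30 | 1.079 | 28% |
| Mean 2,107, assumed CV of sizes 0.69 | 1 + [(1 + 0.69²) × 2,107 − 1] × 0.001 = 4.11 | 0.967 | 33% |

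The stated mean of 2,300 does not equal the stated total divided by 46; the choice between them hardly matters here.

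**3. Simulation with no intervention effect.** The set-up was 46 beta-binomial hospitals sized 830 to 8,600 (total about 97,000, one year of data), with size-ranked pairs randomised within six strata. The analysis was exchangeable logistic GEE adjusted for country and hospital type, with 4,000 to 10,000 trials per scenario. The size distribution, the stratum rates and any ICC above 0.001 are assumptions (ICC range 0.001 to 0.01).

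Country interaction, nominal 5%:

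| Test | Rejection rate |
|---|---|
| Ordinary logistic likelihood ratio, ICC 0.001 | 27–32% |
| Ordinary logistic likelihood ratio, ICC 0.003 | 47–52% |
| GEE Wald, uncorrected sandwich | 7.6–9.2% |
| GEE Wald, Kauermann-Carroll, t on 40 df | 4.6–6.1% |
| GEE Wald, Mancl-DeRouen, t on 40 df | 3.5–4.4% |

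Intervention effect (5 parameters: intercept, arm, country, two for hospital type; 46 − 5 = 41 df):

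| Test | One-tailed 5% | Two-sided 5% |
|---|---|---|
| Uncorrected sandwich, normal reference | 6.2–7.2% | 7.2–8.5% |
| Same, 46 equal hospitals | 6.4–7.2% | 7.3–7.9% |
| Kauermann-Carroll, t on 41 df | 4.9–5.7% | 4.9–5.8% |

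Mancl-DeRouen with t gave 3.6–4.6% two-sided. An unadjusted GEE in the same setting was conservative (1.6% one-tailed, 1.0% two-sided), so these rates belong to the adjusted model that the plan specifies.

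**The case against.** **The plan does not say that it will ignore clustering.** True. It says that its primary analyses account for variability within and between clusters. The 15–33% rates are therefore conditional on one way of filling the gap, and the 15% case uses the smallest hospital size, not the expected one. What remains is that the named test has no counterpart in the named model.

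**Adjusted working-likelihood-ratio statistics for GEE exist.** It would be too strong to say that nothing of the kind can be built. The article names no such adjustment, however, and an ordinary likelihood ratio chi-square is not one.

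**A reader might infer that the primary Wald test is uncorrected and so invalid.** The article does not say that. A condensed article can leave the variance estimator and the reference distribution to a fuller plan. The inflation applies only if no correction is used.

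**A reader might blame the unequal hospital sizes, or quote 7–8% for the planned test.** Neither holds. Equal hospitals give nearly the same inflation, and 7–8% is the two-sided rate, whereas the planned test is one-tailed.

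**A reader might infer that hospital type is wrongly given 1 df.** The article states 1 df only for country, where it is right for two countries. For hospital type it refers only to a similar approach, so 2 df is a clarification and not a correction.

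**Conclusion.** The point holds for the interaction test. The likelihood ratio chi-square cannot be run as written on the GEE model, and it controls whether an overall or a country-specific effect is reported. If an ordinary logistic likelihood ratio filled the gap, the false-positive rate at the protocol's ICC of 0.001 would be about 15% at 830 women per hospital and 27% at 2,107. With unequal sizes it would be about 27–33%, depending on the assumed distribution, and it rises further at a larger ICC.

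For the primary Wald test and its interval the conclusion is conditional. With no small-sample correction, simulated type I error is about 6–7% one-tailed and 7–8% two-sided, mainly because 46 clusters support 5 parameters. That is a reason to state the correction, not evidence of an error in the article. The rates rest on the assumed ICC, size distribution and stratum rates, and are best read as ranges.

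**What to change.** Replace the likelihood ratio test with a robust score or Wald interaction test from the same GEE: 1 df for country and 2 df for the three hospital types. For a Wald test, use a small-sample-corrected sandwich variance, such as Kauermann-Carroll, with a t reference on about 40 df for country (46 hospitals − 6 parameters), and the matching F reference for the 2-df test. The correction has to cover the interaction test as well; otherwise the replacement still rejects at about 8–9%. Mancl-DeRouen is an alternative but was somewhat conservative here, so one of the two should be named in advance.

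State the same correction, on 41 df, for the primary Wald test and its confidence interval, or confirm that the full analysis plan already does so.

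The cost is a few sentences in the analysis plan and standard software options. No data collection changes. The downside is slightly wider intervals.

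### The overall assessment is made to depend on a preliminary interaction test, although the preceding paragraph defines it as the primary analysis without that condition

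*Protocol article*

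**What the plan says.** All references are to the Protocol article.

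- **Statistical analyses, first paragraph.** The primary analyses use GEE logistic regression with the intervention effect adjusted for country and hospital type. All effects are given as odds ratios with 95% CIs and tested one-tailed at 0.05. No condition is attached.
- **Statistical analyses, second paragraph.** A one-degree-of-freedom test of the country-by-intervention interaction is run as a preliminary step. "If the test does not reject the null hypothesis at α = 0.05, the interaction will be eliminated from the final model", and this is what permits the overall effect to be assessed. The contrasting branch is that, after a significant test, "the sub-group analyses will assess the effects of the intervention separately for each country, with a power less than 90" per cent. The approach is repeated for Year 1 mortality, change in mortality within the intervention period, and hospital type.
- **Sample size and power calculations.** The design "allows us to achieve a power of 82% to detect a 30% reduction in the overall rate of maternal mortality", and the calculation is stated "with 2-sided significance test at α = 0.05 and with ρ = 0.001".
- **Hypotheses and Study endpoints.** The single main hypothesis and the primary endpoint both concern overall maternal mortality.

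**The concern.** The second paragraph presents the overall and the country-specific assessments as alternatives, with the data choosing between them. No sentence says that the overall effect is tested and reported in either case, and no separate significance level is set for the country tests.

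Two things are at stake. First, a chance interaction could push aside the question the trial was built to answer and leave two analyses with roughly half the information each. Second, if those analyses were read as tests of whether the programme works, they would add chances of a false-positive claim.

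One modifier makes matters worse. Change in mortality during the intervention period is observed after allocation and can itself be altered by the intervention, so it is a poor basis for deciding which analysis is done.

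The only warning about lost power is the 90% bound, which is already above the 82% stated for the whole trial.

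**Working it through.** **1. Reproduce the stated power.** Inputs from Sample size and power calculations: "an overall maternal mortality rate of 1.5% in the pre-intervention phase"; the number of patients "calculated for an odds ratio of 0.70 and for an intra-cluster correlation coefficient (ρ) of 0.001"; 38,205 women; 830 per hospital; two-sided 0.05.

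- Intervention rate: odds = 0.70 × 0.015/0.985 = 0.01066, so p = 1.055%.
- Design effect: 1 + (830 − 1) × 0.001 = 1.829.
- Effective n per arm: (38,205/2)/1.829 = 10,444.
- Standardised difference: (0.01500 − 0.01055)/√[(0.014775 + 0.010436)/10,444] = 2.866.
- Power: Φ(2.866 − 1.960) = 81.7%. The stated 82% is reproduced. With a one-tailed 0.05 test it would be 88.9%.

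**2. Power in one country.** The split of the 46 included hospitals is not given (23 in Mali and 26 in Senegal were eligible), so 23 per country is assumed.

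| Basis | Two-sided 0.05 | One-tailed 0.05 |
|---|---|---|
| 23 hospitals × 830 women: effective n per arm 5,219, standardised difference 2.026 | 53% | 65% |
| Expected 2006 deliveries (50,144 Senegal; 46,797 Mali), equal clusters: design effects 3.18 and 3.03 | 69-70% | 79-80% |
| Same deliveries, assumed cluster-size CV 0.7, design effect 1 + [(1 + CV²)m − 1]ρ: 4.25 and 4.03 | 57-58% | 69% |

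On the first basis, 20 to 26 hospitals per country gives 47-58% two-sided and 60-69% one-tailed. Every figure is below 90%, and each is well below the power of the whole trial on the same basis.

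**3. How often the country test diverts the analysis.** If the odds ratio is the same in both countries, the interaction test is significant in 5% of trials by construction.

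**4. False claims under no effect anywhere.** Two equally informative, independent country Z statistics were simulated (4 million draws). The overall statistic is (Z1 + Z2)/√2 and the interaction statistic is (Z1 − Z2)/√2; these are independent of each other.

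- Interaction not significant and overall test positive: 0.95 × 0.05 = 4.75%.
- Interaction significant: at least one country is significant at unadjusted 0.05 in 50% of such trials (one-tailed) or 65% (two-sided).
- Total, one-tailed: 4.75% + 5% × 0.50 = 7.25%, about 7.3%.
- Total, two-sided: 4.75% + 5% × 0.65 = 8.0%.

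**5. Under a common odds ratio of 0.70 (two-sided critical value).** Overall-effect claims fall from 81.7% to 77.7% (0.95 × 81.7%). The chance of any claim of benefit is 82.6%. When the interaction test is significant by chance, both countries are significant in only about 1.6% of cases, so a programme that works equally in both would usually be reported as working in one.

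**6. Several tests, illustrative only.** Four independent tests at 0.05 would give at least one significant result with probability 1 − 0.95⁴ = 18.5%. With balanced factors of 2, 2, 2 and 3 levels, the total false-claim rate would be about 14% one-tailed or 17% two-sided. The article gives neither levels for Year 1 mortality or mortality change nor hospital counts by type, and independence is assumed.

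**The case against.** The strongest reply is that the first paragraph already defines an overall, stratification-adjusted primary analysis with no condition, and that the hypothesis and endpoint match it. A reader might infer from the second paragraph that the plan discards its primary answer after a significant interaction. The article does not say so: nowhere is the overall estimate cancelled. That stands. What remains is two adjacent paragraphs that disagree on whether the overall assessment is conditional.

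A reader might also infer that the primary test has an inflated error rate. It does not. A false overall claim occurs in 4.75% of trials under the conditional procedure. The 7.3% arises only if either country's unadjusted result counts as success, a rule the article neither states nor excludes. Alpha control for subgroups is also something a fuller plan might contain.

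Finally, a reader might call the 90% statement wrong, or replace it with a flat 50%. The statement is true, and 50% would be selective: it rests on the minimum cluster size and a two-sided test, while the analysis section specifies one-tailed tests and the article gives larger expected deliveries.

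Examining heterogeneity across a stratification factor is reasonable, and the loss of about four points in overall-effect claims is modest. None of this removes the conflict. The conditional rule is stated explicitly, so it is not detail left to a fuller document.

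**Conclusion.** The concern holds as an inconsistency with a moderate consequence; severity should-fix. The second paragraph of Statistical analyses makes the overall assessment conditional on a preliminary test, against the unconditional primary analysis just before it, and extends the approach to a post-randomisation modifier.

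For the country test alone, the size is a 5% diversion under a homogeneous effect and, on the either-country success rule, a false-claim rate of about 7.3% one-tailed or 8.0% two-sided against 5%. These figures assume equally informative countries. The multi-test figures should not be used as estimates for this trial. Country power runs from about 53% to 80% across the tabulated bases with 23 hospitals per country, so the present wording conveys nothing useful about the loss.

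**What to change.** 1. State that the overall effect adjusted for country and hospital type is the primary analysis, and that it is tested and reported whatever the interaction tests show.
2. Make interactions by country, hospital type and Year 1 mortality secondary, with estimates and CIs for each level.
3. Do not let change in mortality within the intervention period determine which analysis is done.
4. Replace the 90% bound with a range and its basis: about 53% two-sided or 65% one-tailed per country at 23 hospitals × 830 women (split assumed); about 69-70% or 79-80% with expected 2006 deliveries and equal clusters; about 57-58% or 69% with an assumed cluster-size CV of 0.7. The actual split of hospitals should replace the assumption.

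The cost is a change of wording, with no new data and no change to conduct. The one concession is that country-specific results become explicitly secondary.

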**Methods/Design:**

This is an international, multi-centre, controlled cluster-randomized trial of a complex intervention. The intervention is based on the concept of evidence-based practice and on a combination of two approaches aimed at improving the performance of health personnel: 1) Educational outreach visits; and 2) the implementation of facility-based maternal death reviews.

The unit of intervention is the public health facility equipped with a functional operating room. On the basis of consent provided by hospital authorities, 46 centres out of 49 eligible were selected in Mali and Senegal. Using randomization stratified by country and by level of care, 23 centres will be allocated to the intervention group and 23 to the control group. The intervention will last two years. It will be preceded by a pre-intervention one-year period for baseline data collection. A continuous clinical data collection system has been set up in all participating centres. This, along with the inventory of resources and the satisfaction surveys administered to the health personnel, will allow us to measure results before, during, and after the intervention. The overall rate of maternal mortality measured in hospitals during the post-intervention period (Year 4) is the primary outcome. The evaluation will also include cost-effectiveness.

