### Hypotheses

Our hypothesis is that the ALARM International Program (AIP) reduces the overall rate of maternal mortality, as measured in the hospitals in the post-intervention period, by 30% in comparison with the control group. Secondary hypotheses are that the AIP: 1) reduces the number of stillbirths and early neonatal mortality; 2) reduces severe maternal morbidity and the case fatality rate; 3) improves the quality of care through better utilization of local resources and changes in professional practices; and 4) increases the satisfaction of health professionals.

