### Randomization and allocation

Centres were included on the basis of formal, informed consent on the part of the hospital director and the person in charge of maternity services. After a one-year pre-intervention data collection phase, each hospital was randomly assigned, in August 2008, to either an intervention group, in which the AIP will be implemented, or a control group.

The participating hospitals were stratified in six strata corresponding to the combination of two countries (Mali and Senegal) and three hospital types: hospitals in the capital, regional hospitals, and district hospitals outside the capital. We attempted to ensure optimal balance between the hospitals assigned to the intervention and the control groups in terms of their number and size (number of deliveries per year). Therefore, within each stratum, we first ranked the hospitals with respect to size, and then used blocked randomization, with each block of size two containing two hospitals with adjacent ranks, i.e., of similar size (Figure 4). All participating hospitals were randomized simultaneously, after their list was provided, which eliminated any risk of allocation bias.

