**Figure 5 F5:**
[figure not shown]
**Administrative structure for the trial**. *SOGC: Society of Obstetricians and Gynaecologists of Canada.

The trial steering committee meets twice a year to oversee the implementation of the ALARM International Program in the intervention group, follow the data collection process, monitor data quality, coordinate the intermediate statistical analyses, consider the conclusions of the independent committee on data security and monitoring, and coordinate the economic evaluation.

**Start date**: September 1, 2007

**Intervention period**: September 1, 2008 to August 31, 2010

**End date**: August 31, 2011

**Reporting date**: January 1, 2012

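### The change in maternal mortality during the intervention period is listed as an effect modifier, but it is measured after randomisation and is what the programme is meant to alter

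*Protocol article*

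**What the plan says.** The article sets the target as an effect that "reduces the overall rate of maternal mortality, as measured in the hospitals in the post-intervention period, by 30% in comparison with the control group" (Hypotheses), and the abstract confirms the timing: "The overall rate of maternal mortality measured in hospitals during the post-intervention period (Year 4) is the primary outcome". In the section on randomization, "each hospital was randomly assigned, in August 2008", after a baseline year. The trial dates give the intervention period as "September 1, 2008 to August 31, 2010".

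The second paragraph of Statistical analyses begins with a country-by-intervention interaction. Two rules follow. "If the test does not reject the null hypothesis at α = 0.05, the interaction will be eliminated from the final model", and the overall effect is then assessed. Otherwise, "if the interactions are statistically significant, the sub-group analyses will assess the effects of the intervention separately for each country".

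The paragraph then extends this: "A similar approach will be used to test whether the effect of the intervention depends" on three further factors. These are (i) Year 1 mortality, (ii) "ii) on changes in maternal mortality within the intervention period", and (iii) hospital type. No caveat, exploratory label or special method is attached to the second.

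**The concern.** Year 1 mortality, country and hospital type are all fixed before allocation, so within any level of them the arms remain comparable by randomisation. The change during the intervention period is different in kind. It is observed after allocation, it counts the same event as the primary outcome, and it should move if the programme works.

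Sorting or adjusting hospitals by it compares unlike with unlike. Intervention hospitals whose mortality fell include those helped by the programme; control hospitals whose mortality fell did so for other reasons. A contrast between them is no longer the effect of assignment, and a difference in that contrast across levels is not evidence that the programme works better in one kind of hospital. At stake is the meaning of this one effect-modification analysis and of any subgroup statement drawn from it.

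**Working it through.** **1. Order in time**

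| Factor tested | When it is fixed | Can the programme change it? |
|---|---|---|
| Country, hospital type | Before randomisation | No |
| Year 1 mortality | September 2007 to August 2008 | No |
| Change within the intervention period | September 2008 to August 2010 | Yes, by design |
| Primary outcome, Year 4 mortality | September 2010 to August 2011 | Yes |

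**2. The article's planning figures.** The article gives no number for this analysis, so its power statement serves as a check on the inputs. Inputs: control rate 1.5%, odds ratio 0.70, intra-cluster correlation 0.001, 830 women per hospital, 38,205 women in total, two-sided 0.05.
- Design effect = 1 + (830 − 1) × 0.001 = 1.829.
- Effective number per arm = (38,205 / 2) / 1.829 = 10,444.
- Intervention rate at odds ratio 0.70 = 1.055%.
- Power = 81.7%, against the stated 82%. The inputs reproduce.

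The correlation of 0.001 at 1.5% implies a between-hospital coefficient of variation of √(0.001 × 0.985 / 0.015) = 0.256. This was used as the between-hospital SD on the log-odds scale in the model-based simulations. The article gives no figure for how far individual hospitals drift from year to year, so drift is an assumption throughout.

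**3. Mechanism, by hand.** Let θ4 be the true Year 4 log odds ratio, θ23 the mean log odds ratio over Years 2 and 3, and β the within-arm slope of Year 4 log odds on the observed change from Year 1. Then

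conditional log odds ratio ≈ θ4 − β × θ23.

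If drift is a random walk with yearly SD σ, β = 1.5σ² / (1.25σ² + V), where V is the sampling variance of the observed change. With 96,941 / 46 = 2,107 deliveries per hospital per year, about 31.6 deaths are expected in Year 1. Over Years 2 and 3 together, 63.2 are expected (control) or 44.5 (intervention). So V ≈ 1/31.6 + ½ × (1/63.2 + 1/44.5) = 0.051.

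θ4 = ln 0.70 = −0.357. If the effect is immediate, θ23 = −0.357. If it builds up (0.85, 0.75, then 0.70), θ23 = −0.225.

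| Drift SD σ | β | Odds ratio, gradual effect | Odds ratio, immediate effect |
|---|---|---|---|
| 0 | 0 | 0.70 | 0.70 |
| 0.15 | 0.43 | 0.77 | 0.82 |
| 0.25 | 0.73 | 0.82 | 0.91 |

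**4. Simulation, change and its interaction kept in the model** (46 hospitals, uniform true odds ratio 0.70, no true interaction). The arm odds ratio was 0.70 to 0.71 with no drift and ranged from about 0.76 to 0.93 at drift SD 0.15 to 0.25, across implementations and both effect patterns. With a true odds ratio of 1.0 it stayed at about 1.00. The interaction was significant at 0.05 in about 3% to 8% of trials.

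**5. Simulation, hospitals split at the median change** (23 per arm, 2,107 deliveries a year, between-hospital SD 0.3, a persistent hospital-specific shift after Year 1, 2,000 trials per row, true odds ratio 0.70 everywhere).

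| Shift SD | All hospitals | Improved half | Other half | Share in improved half, intervention / control |
|---|---|---|---|---|
| 0 | 0.70 | 0.75 | 0.66 | 79% / 21% |
| 0.2 | 0.70 | 0.80 | 0.75 | 72% / 28% |
| 0.4 | 0.70 | 0.85 | 0.81 | 65% / 35% |
| 0.6 | 0.70 | 0.88 | 0.83 | 61% / 39% |

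With a true odds ratio of 1.0, both halves stayed at about 1.00 in every row and the shares were 50% / 50%. The unequal shares in the table are the selection at work. The undivided comparison is unaffected.

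**The case against.** **The wording may mean something else.** Under Study endpoints, the article says the longitudinal data serve to allow for changes in the indicators over the four years. Item (ii) could be a loose reference to time trends or to an effect that varies by period. This is possible, but the Statistical analyses section does not say it: the sentence makes the change in mortality itself the factor on which the effect may depend. On either reading the same correction is needed, because an arm-by-period model is what a time-course question requires.

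**The biased branch would seldom open.** A non-significant interaction is dropped, and the article does not say that the change itself would then stay in the model. With no true interaction, only about 3% to 8% of trials would reach separate estimates. This stands, and it limits the practical reach. Separate estimates are also spelled out only for country; for item (ii) they follow from the statement that a similar approach applies.

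**Stronger readings the documents do not support.** A reader might infer that the primary result is biased. It is not: the first paragraph of Statistical analyses specifies it separately, as a GEE comparison adjusted for country and hospital type, and the analysis is by intention to treat. Some link remains, since these tests are called preliminary and decide what enters the final model. A reader might also infer that the distortion always runs towards no effect. The zero-shift row shows one half at 0.66, further from 1 than the truth. Nor did the simulations create a false benefit where the programme has no effect.

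**Conclusion.** The point holds in a limited form. Item (ii) is a post-randomisation variable that the programme is designed to change, so estimates within its levels are not randomised comparisons and do not show effect modification. That conclusion rests on the article's own dates and aims and needs no simulation.

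The size does rest on assumptions. It depends on an assumed hospital drift: none gives essentially no shift in the model-based arm odds ratio, and SD 0.15 to 0.25 moves it from 0.70 to roughly 0.76 to 0.93. Median-split strata range from 0.66 to 0.88, so attenuation is usual but not universal. The distortion requires that the programme works. The consequence is confined to a secondary effect-modification analysis; the primary Year 4 comparison stands.

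**What to change.** Delete item (ii) from the list of effect modifiers and keep only those fixed before randomisation: country, hospital type and Year 1 mortality.

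If the intent was to study how the effect develops, replace it with one arm-by-period model that reports the arm effect for Years 2, 3 and 4 with Year 1 as baseline, labelled secondary.

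The cost is one changed sentence and one additional model. The clinical data are already collected continuously in all 46 hospitals, so no new data are needed, and the sample size and primary analysis are unchanged.
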